***CHILD: Mental/Emotional***										
Strengths and Difficulties Questionnaire	30	x					x	x		x

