### Sample size and power

#### Aim 1

We based our primary sample size calculation on previous Family Spirit results indicating small to medium effect sizes for adult and child socio-emotional and behavioral outcomes 6 months post intervention completion [27, 31]. As such, power is based on detecting a small-medium difference between Little Holy One and control participants on caregiver and child outcomes 6-months post intervention completion (see below for power at 24 months post intervention). Since power analysis for mixed-effects regression models is complex, we use the approach described by Hox and Hedges [78, 79]. In this approach there are three steps: 1) estimate the power for a single-level regression model, ignoring clustering. This is considered the target sample size; 2) Compute the actual sample size for the proposed study that ignores the impact of clustering and accounts for attrition; and 3) Generate the effective sample size by penalizing the actual sample size with the design effect formula (i.e., n_eff_ = n / [1 + {n_clus_ – 1} ρ]). If the effective sample size is equal to or larger than the targeted sample size, then power is considered sufficient to detect the effect of interest. In our case, for step 1 power is .80 to detect a medium effect of f = .18 with 120 single-level, independent observations. For step 2, our actual sample size of 120 caregivers and children, with 5 measurement points, yields 600 (non-independent) observations. Accounting for attrition based on our previous work with family-based prevention interventions (i.e., the final *Family Spirit* trial had 18% attrition after 39 months’ intervention) [34], we used a conservative 30% attrition rate and adjusted our actual sample size to 420 non-independent observations. For step 3, using the design effect formula, accounting for 30% attrition and assuming a conservative nesting effect of ρ = 0.3 (to account for additional nesting within schools), our actual sample size of 420 non-independent observations provides the statistical power of 190 independent observations as our effective sample size. The effective sample size is more than the estimate for the targeted sample size indicating sufficient power to detect a small effect (f = .13). Sample size calculations for *all* aims can be found in Table 4**.**

**Table 4 Tab4:** Sample size calculations

	N	α	Power (1-β)	Effect size (f)

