#### 24-month outcomes

While not our primary outcome, based on our conceptual framework, effects on proximal outcomes should correspond to effects on more distal outcomes measured at 2 years post-intervention. As there are no other longitudinal follow-up intervention studies in Native American settings, we assume a very conservative 50% retention rate of our original enrolled sample. This will result in approximately *n* = 42 participants in each arm at *24-months post intervention* completion. With power set to 80% and alpha set to 0.05, with *n* = 42 participants in each arm, and an additional 2 assessment time points, we will be able to detect an average effect size of f = 0.20 (medium effect) on continuous outcome measures between the groups.

#### Aim 2

Using the same approach as our Aim 1 power calculation, we will be powered to detect a medium effect (f = 0.20) in level of perceived stress (PSS) following delivery of the cultural components.

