### Statistical methods

#### Aim 1

The primary effectiveness aim will be assessed on a full intent-to-treat basis. The design incorporates longitudinal measurements that led to a nested data structure. For Aim 1 there are 5 repeated assessments (level-1) nested within children and caregivers (level-2) nested with 4 community health workers (level-3). Given the complexities of nested data, we will use mixed-effects regression models to analyze the data. Mixed-effects regression models are highly flexible and accommodate variability in the number and spacing of assessments within and across participants, continuous and discrete outcome distributions, varied patterns of change over time (e.g., quadratic), and phase-specific change (i.e., discontinuous or piecewise change [79, 81, 82]. To build our outcome models, we will first explore outcome trajectories graphically and descriptively evaluated to determine the best distribution for modeling using “spaghetti plots.” We will then iteratively build our estimation models using the approach described in Singer and Willett [83]. The first model will estimate the proportion of outcome variance at each level; the second model will add growth terms; the third model will add fixed-effect indicators to test for differences in baseline characteristics if necessary [83]. If there are differences in baseline characteristics between the intervention groups, these will be statistically controlled in models that follow. The fourth, and final, model will add the condition indicator (i.e., 0 = WLC, 1 = Little Holy One) and cross-level interaction effects between condition and level-1 terms.

#### Aim 2

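### The Aim 1 power calculation applies 5 measurement points (apparently 7 at 24 months) to every caregiver and child outcome, but Table 3 schedules only four for the SDQ and for several parent outcomes

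*Protocol article*

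**What the plan says.** All places are in the protocol article.

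- **Sample size and power, Aim 1.** One calculation serves both members of the dyad: "our actual sample size of 120 caregivers and children, with 5 measurement points, yields 600 (non-independent) observations". For dropout, "we used a conservative 30% attrition rate and adjusted our actual sample size to 420 non-independent observations". The design effect is applied "assuming a conservative nesting effect of ρ = 0.3", and the result "provides the statistical power of 190 independent observations as our effective sample size". The target it is compared with is that "power is .80 to detect a medium effect of f = .18 with 120 single-level, independent observations". The text ties this power to 6 months after the intervention ends.
- **Table 4.** Parents and children have identical rows: N = 120 and f = 0.13 for Aim 1, N = 84 and f = 0.20 at 24 months.
- **24-month outcomes.** This calculation adds "an additional 2 assessment time points". The total is not printed; 5 + 2 = 7 is an inference, and it agrees with the seven visits that Table 3 gives the primary parent measures.
- **Statistical methods, Aim 1.** The model text repeats the count for both: "For Aim 1 there are 5 repeated assessments (level-1) nested within children and caregivers (level-2" in its notation.
- **Table 3.** The "Strengths and Difficulties Questionnaire" (SDQ) is marked at baseline, 6, 12 and 24 months. The Parenting Practices Interview (PPI), Communal Mastery Scale, Orthogonal Cultural Identification Scale and CESD-R-10 are marked at baseline, 12 weeks, 12 months and 24 months. The PTSD Checklist and Parenting Stress Index are marked at baseline, 6 weeks, 12 weeks, and 6, 12, 18 and 24 months. School attendance has the same seven.

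**The concern.** A power statement that relies on repeated measures depends on how many are taken. The child hypothesis under Aim 1 concerns externalizing and internalizing behavior, and the SDQ is the only instrument listed for it. It never reaches five assessments at any horizon. Nor do the measures of positive parenting, tribal identity and communal mastery, which are the other parent elements of the same hypothesis. The shared count therefore credits these outcomes with observations that the schedule does not collect.

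At stake is how a null result is read. If the SDQ or the PPI shows no difference, a reader will set that against a stated 80% power for a small effect, and may conclude that an effect of that size has been ruled out. The schedule does not support that statement for these outcomes.

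**Working it through.** **Inputs.** From the Aim 1 sample-size text: 120 dyads, 30% attrition, ρ = 0.3, and the formula n_eff = n / [1 + (m − 1)ρ], where m is the number of assessments. From Table 4: α = 0.05, power 0.80. Sidedness is not stated; two-sided is assumed.

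**Reproducing the plan's figure.** 120 × 5 = 600; 600 × 0.70 = 420; 420 / (1 + 4 × 0.3) = 420 / 2.2 = 190.9. This matches the stated 190.

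**Counting from Table 3.**

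| Outcome | By the 6-month visit | To 12 months | In all |
|---|---|---|---|
| SDQ | 2 | 3 | 4 |
| PPI, Communal Mastery, Cultural Identification, CESD-R-10 | 2 | 3 | 4 |
| PTSD Checklist, Parenting Stress Index | 4 | 5 | 7 |
| School attendance | 4 | 5 | 7 |

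So 5 is the 12-month count of the primary parent measures. Even these have only 4 by the 6-month visit.

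**Effective sample size with the real counts.**

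- m = 4: 120 × 4 × 0.70 = 336; 336 / 1.9 = 176.8
- m = 3: 120 × 3 × 0.70 = 252; 252 / 1.6 = 157.5
- m = 2: 120 × 2 × 0.70 = 168; 168 / 1.3 = 129.2

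**Effect of the schedule alone.** Take any effect that has 80% power at n_eff = 190.9. By the normal approximation its power at another n_eff is Φ[(1.960 + 0.842) × √(n_eff / 190.9) − 1.960]. For m = 2: √(129.2 / 190.9) = 0.823; 2.802 × 0.823 − 1.960 = 0.345; Φ = 0.635. The printed f can be rescaled likewise as 0.13 × √(190.9 / n_eff). The last column instead solves the two-arm F test directly (1 numerator df, noncentrality f² × n_eff, 80% power).

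| m | n_eff | Power for an effect with 80% at m = 5 | 0.13 rescaled | Detectable f, F test |
|---|---|---|---|---|
| 5 | 190.9 | 80% | 0.130 | 0.204 |
| 4 | 176.8 | 77% | 0.135 | 0.212 |
| 3 | 157.5 | 72% | 0.143 | 0.225 |
| 2 | 129.2 | 63% | 0.158 | 0.248 |

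The last two columns differ because f = 0.13 does not follow from n = 190: the F test gives 0.204 there, and power at f = 0.13 is 43%. That is a separate error, and it affects every outcome.

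**24-month rows.** Table 4's N = 84 is taken as already net of dropout. With m = 7, n_eff = 84 × 7 / 2.8 = 210.0, and power at f = 0.20 is 82%. With m = 4, n_eff = 84 × 4 / 1.9 = 176.8, and power is 75%; the detectable f moves from 0.194 to 0.212.

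**The plan's own sufficiency rule.** Power is called sufficient if the effective size is at least the target of 120. The lowest value here, 129.2, exceeds 120, so the rule is met at every count.

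**The case against.** Several points limit this, and most of them stand.

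- **The plan's test still passes.** Since 129.2 exceeds 120, the schedule does not overturn the conclusion that the trial meets its target. It undermines only the further claim of 80% power at f = 0.13. That the rule is met is modest reassurance, however: f = 0.18 with 120 independent observations in total gives about 50% power by the same two-sided F test.
- **The affected outcomes are secondary.** The primary outcomes are parental trauma symptoms and parenting stress, and these reach five assessments at 12 months.
- **The window is unclear.** If Table 3 counts months from enrolment, 6 months after a 12-week intervention falls between the 6- and 12-month visits. Two assessments is then the strict count for the SDQ and three the generous one. Comparing 5 with 2 sets a 12-month count against a 6-month count; like for like is 5 against 3, or 4 against 2.

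A reader might infer that only the child rows are wrong, and that the shortfall is larger for children than for parents. The documents do not support this. Four parent outcomes have the same number of assessments as the SDQ in each window, and school attendance, also a child outcome, has seven. A reader might also attribute all of the low power at f = 0.13 to the schedule. In fact power there is already 43% with 5 points; the schedule takes it to 40% with 4 and 31% with 2.

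**Conclusion.** The mismatch is real and can be checked from the printed text: a count of 5 (and, by inference, 7) is applied to all Aim 1 caregiver and child outcomes, while Table 3 gives the SDQ and at least four parent outcomes only four, three or two, depending on the window. The size is moderate. Effective n is 129 to 177 rather than 190, and an effect credited with 80% power has about 63% to 77%. At 24 months the change is small, from 82% to 75% at f = 0.20.

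This rests on the plan's own formula, with 30% attrition, ρ = 0.3, a two-sided test and 7 points inferred for 24 months. It does not show that the trial fails its own sample-size rule, that more participants are needed, or that the problem is confined to children. A further inconsistency in the 24-month text is outside this point: 50% retention of 120 is 60, or 30 per arm, not the 42 per arm used.

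**What to change.** 1. In the Aim 1 sample-size text, state which follow-up window the power refers to and how it maps to the visits in Table 3.
2. There and in the Aim 1 model text, replace the single count of 5 with the number of assessments by outcome group: the primary parent measures, the SDQ, the four-visit parent outcomes and school attendance.
3. In Table 4, recompute the rows for the SDQ and the four-visit parent outcomes from those counts. By the two-sided F test the detectable f is about 0.25, 0.22 and 0.21 for 2, 3 and 4 assessments. Do the same for the 24-month rows, where four assessments with N = 84 give about 0.21.
4. Recompute the 5-point row by the same method (about 0.20, not 0.13). Otherwise the table would set 0.13 beside 0.25, and most of that gap would come from the separate error in f rather than from the schedule.

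Splitting only the child rows from the parent rows is not enough, because it would leave the same count error in the parent rows.

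The cost is wording and a few table rows. No visits or participants are added. The stated detectable effects become less favourable.

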### Lesson frequency and duration

Participants in the intervention group will be taught the 12 lessons over a 16-week period in individual sessions with their community health worker—a delivery strategy selected to enhance participant engagement, local acceptability, and sustainability [47, 48]. Lessons will be delivered at a location that works best for the participant, including Head Start locations, community centers, or study office space at a convenient time (i.e., after drop-off or pick-up). Participants in the control group will participate in group or individual lessons on nutrition at a convenient time and place for participants. Both the intervention and control lessons will begin 2 weeks after study enrollment, and baseline assessments and randomizations have been completed. Participants in both conditions will be assessed by blinded evaluators using mobile data collection at baseline, 12 weeks (when intervention ends), and 6-, 12-, 18-, and 24-months follow-up. Figure 2 outlines the overall flow of the study below.

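### The Aim 1 effective sample of 190 allows only for repeat visits within a person, not for the school nesting it claims to cover or the health-worker level in the Aim 1 model

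*Protocol article*

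**What the plan says.** The Aim 1 part of *Sample size and power* works in steps. It begins with a target: "for step 1 power is .80 to detect a medium effect of f = .18 with 120 single-level, independent observations". It then counts observations: "our actual sample size of 120 caregivers and children, with 5 measurement points, yields 600 (non-independent) observations". After that, "we used a conservative 30% attrition rate and adjusted our actual sample size to 420 non-independent observations". The last step is described as "Generate the effective sample size by penalizing the actual sample size with the design effect formula", which divides n by 1 + (n_clus − 1)ρ. The value of n_clus is not given. The text continues "assuming a conservative nesting effect of ρ = 0.3 (to account for additional nesting within schools", and the result "provides the statistical power of 190 independent observations as our effective sample size". Power is called sufficient if the effective sample is at least the target of 120. The section and Table 4 then give a detectable effect of f = 0.13.

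Under *Statistical methods*, the Aim 1 model has three levels: five assessments, within children and caregivers, "nested with 4 community health workers (level-3". Schools are not a level of that model. Under *Lesson frequency and duration*, intervention participants are taught "in individual sessions with their community health worker".

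**The concern.** The sizing and the analysis describe different clustering. The sizing names schools, the model names workers, and the number itself seems to allow for neither. Correlation between different people in one cluster inflates variance in proportion to the people in that cluster. A design effect built on five visits of one person cannot carry it, however large ρ is made. Two centres take part, so there are on average 60 dyads per school. Four workers would have 15 intervention dyads each if all four teach that arm.

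What is at stake is the stated sensitivity for the primary aim. A reader is told that extra clustering has been paid for. If workers are tied to arms, part of the arm contrast is a contrast between a handful of workers, and more visits per person do not reduce that part.

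**Working it through.** **Inputs from the protocol article.** 120 dyads, 1:1; 5 visits; 30% attrition; ρ = 0.3; target 120; 4 workers; α = 0.05 and power 0.80 (Table 4). Sidedness is not stated; two-sided is assumed here.

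**Reproducing 190.** 120 × 5 = 600, and 600 × 0.7 = 420. With n_clus = 5, 420/(1 + 4 × 0.3) = 420/2.2 = 190.9. Solving back from 190 gives n_clus = 5.04. Other cluster sizes do not give 190:

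| n_clus | 420/[1 + (n_clus − 1) × 0.3] |
|---|---|
| 3.5 | 240 |
| 5 | 190.9 |
| 6 | 168 |
| 15 | 81 |
| 30 | 43 |
| 60 | 22 |

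So the arithmetic is right, and the only clustering it covers is visits within a person.

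**Detectable effect without a worker term.** For a two-group comparison (1-df F test, noncentrality f²N), 80% two-sided power at N = 190.9 needs f ≈ 0.204. At the printed f = 0.13, power is about 43%. This gap exists before any worker effect.

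**Adding the worker level.** Let m = 5 visits, k = people per worker and r = worker ICC (assumed, as the article gives none), with r counted inside the 0.3. The design effect for an arm clustered by worker is

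DE = 1 + (m − 1) × 0.3 + m(k − 1)r = 2.2 + 5(k − 1)r.

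Retention of 70% leaves 42 people and 210 observations per arm, which matches the 420.

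- Four workers in the intervention arm only: k = 42/4 = 10.5, and the control DE stays at 2.2. Then n_eff = 840/(2.2 + 2.2 + 47.5r).
- Two workers per arm: k = 42/2 = 21. Then n_eff = 420/(2.2 + 100r).

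| Worker ICC | Four in one arm: n_eff | f at 80% power | Two per arm: n_eff | f at 80% power |
|---|---|---|---|---|
| 0 | 190.9 | 0.204 | 190.9 | 0.204 |
| 0.01 | 172 | 0.215 | 131 | 0.246 |
| 0.02 | 157 | 0.225 | 100 | 0.283 |
| 0.05 | 124 | 0.254 | 58 | 0.373 |

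The effective sample falls to 120 at r = (840/120 − 4.4)/47.5 = 0.055 with four workers in one arm, and at r = (420/120 − 2.2)/100 = 0.013 with two per arm.

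**Sensitivity to convention.** Using enrolled numbers for k (60/4 = 15) in the one-arm case gives n_eff = 840/(4.4 + 70r) = 165, 145 and 106, crossing 120 at r = 0.037. Retained numbers are preferred here because they agree with the 420 observations. None of these figures includes the further loss from having only 2 or 3 degrees of freedom between workers.

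**The case against.** The only sentence that is untrue of the calculation concerns schools, and school nesting needs no penalty, because site is a stratification factor (*Allocation, concealment, and implementation*) and so largely cancels from the arm contrast. That is correct, and it makes the school half a matter of wording.

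The worker half depends on workers being tied to arms, which the article never says. The abstract can be read as community health workers teaching both arms. *Control condition* and *Intervention fidelity* speak of interventionists for control sessions too, and the Aim 1 model nests all participants, not one arm, within the 4 workers. Against that, *Lesson frequency and duration* mentions the community health worker only for the intervention arm. The question is open, and with shared workers and a constant effect nothing is lost.

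Even with four workers in the intervention arm only, the effective sample on retained numbers (172 to 124) stays above the plan's target of 120. The exact handling of the worker term may also properly sit in an analysis plan that is not shown.

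These points limit the consequence. They do not repair the statement about what ρ = 0.3 covers, or the mismatch between a two-level sizing and a three-level model.

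**Conclusion.** The point holds on the document alone in two respects. The effective sample of 190 penalises only repeat visits, contrary to the text, and the model's third level is absent from the sizing. The size of any loss is conditional on an assumed worker ICC and an unstated split of workers by arm: none if workers are shared and the effect does not vary by worker, modest with four workers in one arm, and serious with two per arm once the ICC exceeds about 0.013.

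A reader might infer three stronger things that the document does not support:

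- That worker clustering leaves the trial underpowered. The article does not tie workers to arms, and one of the two arm-tied cases still meets the plan's own criterion on retained numbers.
- That 190 is miscalculated. It reproduces; what is wrong is its description.
- That worker nesting explains the whole step from f = 0.13 to 0.21 or more. Most of the step to 0.21–0.25, from 0.13 to 0.204, is a separate error in the printed effect size.

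**What to change.** - Delete the claim that ρ = 0.3 covers additional nesting. State n_clus = 5 and describe 190 as the effective sample of a two-level analysis (visits within person).
- State whether the 4 workers teach one arm or both, and make the sizing agree with the Aim 1 model.
- If the same workers teach both arms, fit worker as a fixed effect (3 indicators). The two-level n_eff of about 190 then stands, provided the effect does not vary by worker, but report the detectable effect as about f = 0.20 at 80% two-sided power. Do not carry the printed 0.13 forward.
- If workers are tied to arms, restate the detectable effect with a worker term over an ICC of 0.01 to 0.05, labelled as an assumption: about f = 0.21 to 0.25 with four workers in the intervention arm only, or about 0.25 to 0.37 with two per arm. Use small-sample degrees of freedom, and allow also for the control-arm group sessions of up to 7–8 dyads (*Control condition*). A model that treats controls as unclustered would leave these out.

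The cost is a change of wording, a restated figure and a small change to the mixed model, with no more participants or staff. The downside is that the stated detectable effect becomes less favourable.

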**Aim 1**				
Parents	120	0.05	0.80	0.13
Children	120	0.05	0.80	0.13
**24-month outcomes**				
Parents	84	0.05	0.80	0.20
Children	84	0.05	0.80	0.20
**Aim 2**				
Parents	60	0.05	0.80	0.20
**Additional moderator exploration**				
Gender (Child outcomes)	60	0.05	0.80	0.24
Age (Child outcomes)	60	0.05	0.80	0.24
Type of caregiver (Parent and child outcomes)	60	0.05	0.80	0.24

#### 24-month outcomes

While not our primary outcome, based on our conceptual framework, effects on proximal outcomes should correspond to effects on more distal outcomes measured at 2 years post-intervention. As there are no other longitudinal follow-up intervention studies in Native American settings, we assume a very conservative 50% retention rate of our original enrolled sample. This will result in approximately *n* = 42 participants in each arm at *24-months post intervention* completion. With power set to 80% and alpha set to 0.05, with *n* = 42 participants in each arm, and an additional 2 assessment time points, we will be able to detect an average effect size of f = 0.20 (medium effect) on continuous outcome measures between the groups.

#### Aim 2

Using the same approach as our Aim 1 power calculation, we will be powered to detect a medium effect (f = 0.20) in level of perceived stress (PSS) following delivery of the cultural components.

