### Trial design

This is a randomized controlled trial (RCT) with 1:1 randomization of 120 parent-child dyads to Little Holy One or an active control group. Within the RCT there is an embedded single-case experimental design (SCED) aimed at exploring the added impact of specific cultural components [38].

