#### Additional planned analysis

We will explore moderation of intervention effects by gender and age of the child, and type of caregiver. We are not measuring sex as a biological variable, so our analysis of sex differences is limited by a self-report gender of child indicated at baseline interview. While our aims are not powered to detect moderation effects, exploration of moderation in this RCT will serve as hypothesis generating and identify potential differing effects by gender and age to explore in future studies with larger sample sizes [80]. Moderators will be explored by adding a three-way interaction term to the models (e.g., Intervention Arm X Time X Moderator). This three-way interaction coefficient indicates whether change in average outcome varies by levels of the moderator while controlling for change in the control group. When a three-way interaction term is significant, we will re-estimate the models, stratified by level of the moderator, to generate strata-specific effect sizes. Using the gender model as an example, and significance set to *p* = 0.05, assuming ~ 50% of our child sample will be male, with our sample size of *n* = 30 male and *n* = 30 female children enrolled in Little Holy One, we will have 80% power to detect a medium (f = .24) difference in intervention effects between genders.

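### The 24-month power row states 50% retention but uses the n for 70%, and the moderator rows give 80% power for a within-arm comparison, not the planned interaction

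*Protocol article*

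**What the plan says.** The Trial design section specifies "1:1 randomization of 120 parent-child dyads to Little Holy One or an active control group", so 60 dyads per arm.

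Under 24-month outcomes the protocol article says "we assume a very conservative 50% retention rate of our original enrolled sample". The next sentences take this to give about "42 participants in each arm, and an additional 2 assessment time points". "With power set to 80% and alpha set to 0.05", they put the detectable average effect at f = 0.20. Table 4 repeats this as N = 84, power 0.80 and f = 0.20, for parents and for children.

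Under Additional planned analysis, moderation is to be tested by an Arm × Time × Moderator term that allows for change in the control group. The section opens its power remarks with "While our aims are not powered to detect moderation effects" and calls the work hypothesis generating. It then takes 30 boys and 30 girls in Little Holy One and concludes "we will have 80% power to detect a medium (f = .24) difference in intervention effects between genders". Table 4 prints N = 60, power 0.80 and f = 0.24 for child gender, child age and type of caregiver.

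**The concern.** The two parts of the 24-month statement cannot both be true. The retention rate is applied to the enrolled sample, so no other denominator is available, and rounding cannot turn 30 into 42. The 84 in Table 4 shows that the 42 is not an isolated misprint. It equals what remains of 120 after the 30% attrition assumed for Aim 1.

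In the moderator rows, the sample counted does not match the effect claimed. A comparison of boys and girls within one arm is not a difference in intervention effects. The latter also needs the boy–girl contrast in the control arm, with its own sampling error. The paragraph also both disclaims power and claims 80%.

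At stake is how null 24-month and moderator results are read. A reader relying on Table 4 would believe that effects of the printed sizes would probably have been found. Enrolment, randomisation and the Aim 1 analysis are not affected.

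**Working it through.** **Inputs from the protocol article**
- 120 dyads, 1:1 (Trial design).
- 5 measurement points, ρ = 0.3, 30% attrition, and effective n = observations / [1 + (points − 1)ρ] (Sample size and power, Aim 1).
- 2 additional assessments for the 24-month row, so m = 7.
- α = 0.05.

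**Assumptions:** the test is two-sided; ρ = 0.3 carries over from Aim 1; m from 5 to 7 is shown as a range.

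**1. Retention**
- 50% × 60 = 30 per arm, 60 in total.
- 42 / 60 = 84 / 120 = 70%.

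**2. Reproducing the 24-month row**

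Use a two-group F test with noncentrality λ = N·m·f² / [1 + (m − 1)ρ] and df 1, N − 2. For N = 84, m = 7: effective n = 588 / 2.8 = 210, and λ = 210 × 0.04 = 8.4.

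| N retained | m = 7 | m = 6 | m = 5 |
|---|---|---|---|
| 84: power at f = 0.20 | 0.82 | 0.80 | 0.78 |
| 60: power at f = 0.20 | 0.67 | 0.66 | 0.63 |
| 60: f detectable with 80% power | 0.233 | 0.237 | 0.244 |

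The published row therefore reproduces, but with 84 retained. For N = 60, m = 7, effective n is 420 / 2.8 = 150 and λ = 6.0. A normal approximation for 30 per arm gives 0.69 (m = 7) and 0.65 (m = 5), hence the range 63–69%. With this method about 40 to 44 per arm are needed for f = 0.20.

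**3. Reproducing the moderator row**
- Within Little Holy One, 30 v 30, m = 5, no attrition: effective n = 300 / 2.2 = 136, or 68.2 per group.
- On the two-group scale f = .24 is d = 2f = 0.48 SD.
- SE = √(2 / 68.2) = 0.171; 0.48 / 0.171 = 2.80; power = 0.80 (0.79 by the F test).

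This matches the stated figure.

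**4. The planned interaction**

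The contrast (boys − girls in Little Holy One) − (boys − girls in control) has four cells of 30, so its variance is twice that of the within-arm comparison.
- No attrition: SE = √(4 / 68.2) = 0.242; 0.48 / 0.242 = 1.98; power 0.51. Detectable difference 2.80 × 0.242 = 0.68 SD.
- 30% attrition (21 per cell, effective 105 / 2.2 = 47.7): SE = √(4 / 47.7) = 0.289; 0.48 / 0.289 = 1.66; power 0.38. Detectable difference 2.80 × 0.289 = 0.81 SD.

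**The case against.** A reader might infer that neither stated 80% power is delivered. The article does not support that, for these reasons.

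- **Both figures follow from the n they use.** If 70% retention was intended, the 24-month power stands and the retention sentence is the slip. That the 42 was carried over from Aim 1 is an inference from matching numbers.
- **The 24-month shortfall is not forced even at 50% retention.** The 63–69% drops half the sample from every assessment. Suppose instead that the Aim 1 loss applies to the first five points (420 observations) and 60 people attend each of the two added ones. That gives 420 + 120 = 540 observations, effective n = 540 / 2.8 = 193, and power of about 0.79 for f = 0.20. The mixed models would accept such data. The article does not describe this reading, and its own shortcut applies attrition flatly, but it shows that the lower figure is conditional.
- **Another test would give another answer.** A group-by-time F test would have power above 0.9 for f = 0.20 at 30 per arm. The article describes the design-effect approach, not that test.
- **The scale of f = .24 is undefined.** If it is the interaction's own f in a four-cell model with all 120, the difference in effects is 0.96 SD and power with no attrition is about 0.98. The two-group scale is more plausible because it reproduces the row.
- **The stakes are limited.** The 24-month outcome is described as not primary, and moderation as unpowered and hypothesis generating.

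These points limit the size of the problem. They do not reconcile 50% with 42 per arm, nor turn a within-arm comparison into a difference in intervention effects. The disclaimer on moderation also does not appear in Table 4, which prints 0.80 for three moderators.

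**Conclusion.** The point holds as two internal inconsistencies, with conditional consequences for power.

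For 24 months, either the retention rate or the N and f are wrong. If 50% is meant and applies at every assessment, power for f = 0.20 is about 63–69% and the detectable f is about 0.23–0.24. This rests on ρ = 0.3, two-sided α of 0.05 and 5 to 7 points. If 70% is meant, about 80% power stands.

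For moderation, the 80% claim describes a different comparison from the planned interaction and contradicts the statement that moderation is not powered. If f = .24 denotes a 0.48 SD difference in effects, power is about 51% with no attrition and 38% with 30%, and the detectable difference is about 0.68–0.81 SD.

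Because the rows concern a secondary time point and exploratory analyses, this should be fixed but is not critical.

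**What to change.** State one retention figure and make the text and Table 4 agree with it:
- 50%, with N = 60 (30 per arm) and a detectable f of about 0.23–0.24, recomputed for the number of assessments each outcome has. In Table 3 the child SDQ has only four, which gives 60 × 4 / 1.9 = 126 effective observations and f of about 0.25.
- Or 70%, with N = 84 and f = 0.20, removing the 50% figure and its description as very conservative.

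For moderation, either recompute the rows as an interaction using both arms and attrition, with the scale of the effect size defined, or delete the 80% power sentence and the Table 4 rows and keep the statement that moderation is unpowered and hypothesis generating.

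The cost is wording and Table 4 only. Design, enrolment and analysis stay the same. Unless the 70% option is taken and the moderator rows are simply removed, the printed figures become less favourable.
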